## Abstract

**Background:**

Rates of dementia for Aboriginal and Torres Strait Islander peoples are three to five times greater compared to non-Indigenous Australians, with earlier age of onset. However, the risk and protective factors that drive these higher rates vary across existing cohort studies, with minimal findings on the role of vascular risk factors beyond stroke. Harmonisation of data across studies may offer greater insights through enhanced diversity and strengthened statistical capabilities. This study aims to combine three landmark cohort studies of Aboriginal and Torres Strait Islander participants to better understand the determinants of cognitive health and dementia.

**Methods/design:**

Three cohort studies - the Kimberley Healthy Adults Project (KHAP, *N* = 363), Koori Growing Old Well Study (KGOWS, *N* = 336) and Torres Strait Dementia Prevalence Study (TSDPS, *N* = 274) - share a similar research methodology with demographic, medical history, psychosocial factors, cognitive tests and consensus clinical diagnoses of cognitive impairment and dementia. Associations between risk and protective factors of interest and the presence of dementia and/or cognitive impairment diagnoses will be evaluated by univariable and multivariable logistic regression in a harmonised cross-sectional cohort of 898 participants. Factors associated with incident dementia and/or cognitive impairment will be assessed in a subset of KHAP (*n* = 189) and KGOWS participants (*n* = 165) who were available in longitudinal follow-up, after exclusion of those with baseline dementia or cognitive impairment. Analyses in relation to outcome measure of death or dementia will be conducted to account for the competing risk of death. Logistic regression will be used to evaluate the association between the individual components of the 16-component Kimberley Indigenous Cognitive Assessment (KICA) tool and the presence of dementia and cognitive impairment determined by independent consensus diagnoses. Multivariable binary logistic regression will be used to adjust for the effect of confounding variables. Results will be reported as odds ratios (OR) with 95% confidence intervals (95% CI).

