## Methods/design

### Design

The KHAP study was undertaken from 2004 to 2006 and involved 363 Aboriginal participants aged 45 and older from different communities in the remote Kimberley region of WA [1]. The KGOW study recruited 336 participants aged 60 and older from five Aboriginal communities, two from metropolitan Sydney and three in regional coastal areas of NSW between 2010 and 2012 [14]. Follow-up of participants occurred after six and seven years for KGOWS-II and KHAP wave 2, respectively. The TSDP study was conducted between 2015 and 2018 and recruited 274 participants aged 45 and older from five mainland and 18 island communities across the Torres Strait and Northern Peninsula [3]. A summary of the studies and number of participants is provided in Table 1. All three cohort studies worked in partnership with local community organisations and Aboriginal and Torres Strait Islander members and researchers to support recruitment, data collection, and feedback to communities to ensure culturally safe engagement with participants. Risk factors were collected using a structured interview protocol and encompassed demographic, medical, and psychosocial factors collected from participants and family carers where available. This comprehensive assessment was independently evaluated by a panel of clinical specialists to establish clinical diagnoses by consensus. All three cohort studies used the KICA, a screening tool for older Aboriginal and Torres Strait Islander peoples, that was validated in the remote Kimberley region of WA [15], modified for urban and regional dwellers in the form of the mKICA [16] and adapted for the Torres Strait [17]. A shortened version (KICA-Screen) has been validated for face-to-face and telehealth administration [17, 18].

**Table 1 Tab1:** Descriptive summary of landmark studies

Study/Cohort	Location	Age (years)	Sample Size (*N*=)	Participants (*n*=)
Kimberley Healthy Adults Project (KHAP)				
Wave 1 (W1) 2004–2006 [1, 8]	Remote WA	≥ 45	363	289 with normal cognition; 45 with dementia; 29 with CIND*.
Wave 2 (W2) 2011–2013 [9]	Remote WA	≥ 45	398‡	. Of 363 W1 participants, 184 completed all W2 assessments, 5 had cognitive assessment only, 109 had died and 65 declined to participate or could not be located. 105 new participants were recruited at W2. W2 cohort: 226 with normal cognition; 29 with dementia; 33 with CIND; 1 missing diagnosis; had 109 died.
Koori Growing Old Well Study (KGOWS)				

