Wave 1 (W1) 2010–2012 [2, 14, 19]	Urban & Regional NSW	≥ 60	336	249 with normal cognition; 45 with dementia; 38 with MCI†; 4 with other cognitive disorder.
Wave 2 (W2) 2016–2018 [20]	Urban & Regional NSW	≥ 60	233‡	Of 336 W1 participants, 165 were followed-up, 68 had died and 103 did not participate. W2 cohort: 105 with normal cognition; 10 with dementia at baseline; 16 with incident dementia; 34 with MCI; 68 had died.
Torres Strait Dementia Prevalence Study (TSDPS)				
Wave 1 (W1) 2015–2018 [3, 12]	Torres Strait	≥ 45	274	175 with normal cognition; 39 dementia; 60 CIND.

CIND = Cognitive Impairment No Dementia; MCI = Mild Cognitive Impairment; NSW = New South Wales; WA = Western Australia

*CIND is defined as those with a decrement in cognitive functioning that met DSM-IV-TR criteria for a cognitive or amnestic disorder but without significant loss in activities of daily living (ADL) and not attributable to a psychiatric illness or intellectual disability

† MCI diagnoses in the KGOW cohort were reclassified as CIND based on DSM IV-TR diagnoses in line with the other cohorts for analyses

‡ Sample sizes include those who have died

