#### Data harmonisation

Data will be harmonised using the Stata statistical package (StataCorp, College Station, Texas), version 17. Variables of interest will be recoded to be consistent across datasets prior to combination into a single final dataset. Data harmonisation utilises the best available information. This means that patient self-reports for a given variable may be corroborated by information from family reports, medications, primary care software derived medical history and medications where available. For instance, the variable diabetes combines self-reports of the condition (yes/no), family informant reports of the condition (yes/no), and medication history (diabetic medication by self-reports or in medication review). Medication lists available for the participants will be coded using the World Health Organization’s Anatomical Therapeutic Chemical (ATC) Classification and allow for sub-analyses of outcomes in relation to medication categories of interest such as anticholinergics, analgesics, anti-psychotics and so forth [33]. The full details of variables of interest in the pooled cross-sectional dataset are provided in the appendices (Appendix 1.1).

Based on the variables of interest available in each dataset (Table 2), KHAP wave 2, KGOWS-I and TSDPS will be harmonised in cross-section, with a combined cohort of 898 Aboriginal and Torres Strait Islander participants, 244 (27%) of whom will have a diagnosis of dementia or CIND/MCI. For longitudinal analyses, data from KHAP wave 1 will be harmonised with KGOWS-I and combined with diagnoses at baseline (wave 1) and follow-up (wave 2) for analysis of factors of interest in a smaller subset of 354 participants as summarised in the appendices (Appendix 1.2). There is no longitudinal data available for TSDPS at the present time.

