#### Data analyses

Data will be analysed using the Stata statistical package (StataCorp, College Station, Texas), version 17. Analyses will be performed on harmonised cross-sectional and longitudinal data. Associations between risk and protective factors of interest and the presence of dementia and/or cognitive impairment based on consensus diagnoses will be evaluated by univariable and multivariable binary logistic regression. Analyses by dementia subtype will also be conducted to ascertain risk factors of importance between groups. In the longitudinal cohort, risk factors of interest will be determined from baseline measures (W1), compared with consensus diagnoses at follow-up (wave 2) and analysed in relation to outcome measures of incident dementia and/or cognitive impairment using univariable and multivariable logistic regression. To account for the competing interest of death (*n* = 177 before wave 2 follow-up), multinominal logistic regression will be used to estimate the association between variables of interest and the following outcomes: (1) neither cognitive impairment nor dementia nor died; (2) cognitive impairment or dementia during the study; and (3) death between baseline and follow-up. Results will be reported as odds ratios (OR) with 95% confidence intervals (95% CI). Multivariable binary logistic regression will be used to adjust for the effect of confounding variables that are anticipated to be associated with dementia such as age, sex, education and study cohort. Variables that are significant in univariable analyses will be entered into a multivariable model, after which a process of clinical judgement and examination of measures including the Akaike and Bayesian information criteria will be employed to decide which variables to retain in the final multivariable model.

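### The longitudinal N of 354 (189 + 165) is labelled as after exclusion of baseline impairment, but Table 1 shows it is the count before exclusion; the 177 deaths are also a full-cohort count

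*Protocol article*

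**What the plan says.** The Methods/design paragraph of the abstract gives 189 KHAP and 165 KGOWS participants as those "who were available in longitudinal follow-up, after exclusion of those with baseline dementia or cognitive impairment". The Data harmonisation section adds the two and describes the "analysis of factors of interest in a smaller subset of 354 participants", referring to Appendix 1.2, which is not available here.

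Table 1 gives the flow behind both numbers:

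- **KHAP wave 1:** "289 with normal cognition; 45 with dementia; 29 with CIND".
- **KHAP wave 2,** accounting for all 363 wave 1 participants: "184 completed all W2 assessments, 5 had cognitive assessment only, 109 had died and 65 declined to participate or could not be located".
- **KGOWS wave 1:** 249 normal, 45 dementia, 38 MCI and 4 other cognitive disorder, 336 in all.
- **KGOWS wave 2:** 165 followed, 68 died and 103 not taking part, again out of all 336. The wave 2 cohort is "105 with normal cognition; 10 with dementia at baseline; 16 with incident dementia; 34 with MCI; 68 had died".

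The Data analyses section specifies binary logistic regression for incident dementia and/or cognitive impairment. It then adds a three-outcome multinomial model, introduced with "To account for the competing interest of death" and a count of 177 deaths before wave 2. Neither that section nor Data harmonisation repeats the baseline exclusion given in the abstract.

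**The concern.** Incidence can be estimated only in people free of the outcome at baseline. The abstract says the exclusion has been made and attaches 189 and 165 to the result, yet Table 1 places people with baseline dementia inside one of those figures and derives the other from the whole wave 1 cohort. The label and the numbers cannot both be right.

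At stake is the size of the analysis set for the second primary objective, the longitudinal one. A reader judging how many predictors the incident-outcome models can carry would start from a number that is too large. The same applies to the competing-risk model: its deaths are quoted as a full-cohort count, and the text does not say that the model is confined to people at risk at baseline. This matters because the Background criticises the earlier analyses of KHAP and KGOWS for not accounting for mortality.

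**Working it through.** All inputs are from Table 1 unless stated.

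**1. Reproduce the stated figures.**

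- KHAP followed: 184 + 5 = 189, and 363 − 109 − 65 = 189.
- KGOWS followed: 336 − 68 − 103 = 165, and 105 + 10 + 16 + 34 = 165.
- Sum: 189 + 165 = 354, as in Data harmonisation.
- Deaths: 109 + 68 = 177, as in Data analyses.

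Every figure reproduces, but only when the starting point is the full wave 1 cohort: 184 + 5 + 109 + 65 = 363 and 165 + 68 + 103 = 336.

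**2. Count those impaired at baseline.**

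- KHAP: 45 + 29 = 74, leaving 289 normal.
- KGOWS: 45 + 38 + 4 = 87, leaving 249 normal. If the four with other cognitive disorders are not counted as impaired, 83, leaving 253.
- Both: 161 (or 157) of 363 + 336 = 699. At-risk pool: 289 + 249 = 538 (or 542).

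The choice about the four is open. The cross-sectional total of 244 with dementia or CIND/MCI in Data harmonisation equals (29 + 33) + (45 + 38) + (39 + 60) = 62 + 83 + 99, which leaves them out.

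**3. Bound the number at risk and followed up.**

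| | Maximum | Minimum |
|---|---|---|
| KHAP | 189 (none of the 74 re-examined) | 189 − 74 = 115 (all re-examined) |
| KGOWS | 165 − 10 = 155 | 155 − 42 = 113, or 155 − 38 = 117 without the four |
| Total | 344 | 228, or 232 |

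The KGOWS rows take the tabulated 10 as all the baseline dementia cases that were followed. The stated 354 is too large by at least 354 − 344 = 10 and at most 354 − 228 = 126.

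**4. Deaths.** The 177 are counted over 699 people, 161 (or 157) of them impaired at baseline. Table 1 does not split deaths by baseline diagnosis. In KHAP, at least 109 − 74 = 35 of the deaths were in people normal at baseline. In KGOWS no positive minimum follows, because the 87 − 10 = 77 impaired participants who were not followed outnumber the 68 deaths. How many of the 177 fall outside the at-risk pool is unknown.

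**5. The five cognitive-only KHAP participants.** The KHAP wave 2 diagnoses sum to 226 + 29 + 33 + 1 = 289 = 184 + 105, that is, the full completers plus the new recruits. The five are counted in the 189 but have no tabulated wave 2 diagnosis.

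**The case against.** The abstract does state the exclusion, the Data analyses section names incident outcomes, baseline diagnoses are carried into the longitudinal dataset, and Table 1 itself separates baseline from incident dementia in KGOWS. The abstract sentence could also be read as 189 and 165 available, with the exclusion still to come. On that reading the rule is sound and only the analysed N is unstated, possibly given in Appendix 1.2.

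Much of this stands. A reader might infer that prevalent cases will be analysed as incident, or that deaths of people already demented will fill the death category. The article does not show either. The 177 is offered as a count of deaths, and nothing says that all of them enter the model.

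A reader might also scale by wave 1 frequencies: 189 × 289/363 + 155 × 249/291 = 150 + 133 = 283, an overstatement of 71 (20%). That assumes follow-up did not depend on baseline diagnosis in KHAP, or on MCI or other impairment in KGOWS. KGOWS speaks against it: 10 of 45 with baseline dementia were followed (22%), against 155 of the other 291 (53%). Applying that ratio (about 0.42) to the KHAP dementia cases, also an assumption, gives about 162 + 133 = 295, an excess of 59 (17%). Neither figure is established.

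The charitable reading does not remove the inconsistency. Data harmonisation gives 354 as the subset for analysis, not as a pool awaiting exclusion, and on any reading 165 with 10 baseline dementia cases inside it is not a post-exclusion count.

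**Conclusion.** The point holds as a wrong sample size for a primary objective. For KGOWS the contradiction is direct and needs no assumption. For KHAP, 189 is by construction the follow-up count of the whole cohort, and it would equal the post-exclusion count only if none of the 74 impaired at baseline had been re-examined.

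The document establishes an overstatement of at least 10. The at-risk, followed-up N lies between 228 (or 232) and 344. The lower end requires every impaired KHAP participant to have survived and been re-examined, so it is an arithmetic limit, not a likely value.

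On deaths the conclusion is narrower: 177 is a full-cohort count, and the exclusion is not restated for either longitudinal model. The article does not support going further and saying that the incident or death odds ratios will be contaminated by prevalent cases. It needs correcting because the text leaves the analysis set ambiguous and the correction is cheap.

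**What to change.** 1. In Data harmonisation and Data analyses, state that both the binary and the three-outcome longitudinal models are restricted to participants with normal cognition at wave 1.
2. State how the four KGOWS participants with other cognitive disorders are classified. The at-risk pool is 538 if they are excluded and 542 if they are kept.
3. Within that pool, report by cohort how many were re-examined with a consensus diagnosis, how many died and how many were not followed.
4. Replace 354 (189 + 165) and 177 with those counts throughout, including the abstract, or keep them and label them plainly as full-cohort counts before exclusion.
5. Say whether the five cognitive-only KHAP participants have a wave 2 consensus diagnosis, and count them among the re-examined only if they do.

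The cost is a recount from data already held and a few corrected sentences. The downside is a smaller stated longitudinal N.

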**Discussion:**

Greater understanding of risk and protective factors of dementia and cognitive impairment relevant to Aboriginal and Torres Strait Islander peoples may improve approaches across the life course to delay cognitive decline and reduce dementia risk.

**Supplementary Information:**

The online version contains supplementary material available at 10.1186/s12883-024-03688-y.

## Background

Survivorship among Aboriginal and Torres Strait Islander peoples is increasing, with many living long and healthy lives. At the same time, rates of cognitive impairment and dementia for Aboriginal and Torres Strait Islander peoples are three to five times greater compared to non-Indigenous Australians, with earlier age of onset [1–3]. Aboriginal and Torres Strait Islander people’s health and wellbeing is multifaceted and shaped by historical, cultural, political and socioeconomic dimensions. The legacy of colonisation and austere government policies have ongoing repercussions for many older Aboriginal and Torres Strait Islander peoples, some (estimated 1 in 7 over the age of 50) of whom are from the Stolen Generation - children forcibly removed from their families and raised in institutions, foster homes or adopted by non-Indigenous families between 1910s and 1970s [5]. Non-communicable and chronic diseases contribute much to the disparities in life expectancy between Aboriginal and Torres Strait Islander peoples and non-Indigenous Australians, which has only decreased marginally over the last decade from approximately 10 to 8 years [6, 7]. More is needed to promote brain health and ageing in this unique population over the life-course.

Three landmark Australian studies involving Aboriginal and Torres Strait Islander cohorts from Western Australia (WA), New South Wales (NSW), and the Torres Strait in Far North Queensland have researched factors associated with dementia. In a cross-sectional study of 363 Aboriginal people aged 45 years and older living in the remote Kimberley region of WA, dementia was associated with smoking, stroke, epilepsy, head trauma, poor mobility, incontinence and falls, after adjustment for age, sex and education. On follow-up, only age and head trauma endured as longitudinal risk factors for cognitive decline [8, 9]. In a cohort of 336 participants in the major city of Sydney and regional NSW, multivariable analysis highlighted age, childhood trauma, unskilled work, stroke and head injury as independent predictors of all-cause dementia alongside comorbid factors such as depression, current high risk alcohol use, low Body Mass Index (BMI), mobility impairment, functional impairment, incontinence, hospitalization in the past year, residing in residential care, social isolation and low physical activity levels [2, 10]. Older age, male sex, unskilled work history, and polypharmacy were associated with incident dementia and Mild Cognitive Impairment (MCI) [11]. On follow-up, age, male sex, unskilled work, polypharmacy and Apolipoprotein E allele 4 (APOE ε4) were longitudinal risk factors for cognitive decline. However, similar to the Kimberley study, the competing risk of mortality was not taken into consideration, which likely impacted these longitudinal results [9]. In the Torres Strait, cerebrovascular disease, chronic kidney disease, and older age were significantly associated with dementia in a cohort of 274 participants [12]. Vascular risk factors other than stroke, such as diabetes and hypertension, were not associated with dementia in any of the cohorts, possibly due to the ubiquity of these conditions, non-linear risk relationships or limited statistical power. This is consistent with the findings of a recent systematic review that highlighted the limited data on risk factors for vascular dementia and a lack of geographical representation for many risk factors for dementia [13].

### Study aims

The aim of this research is to elucidate risk factors associated with cognitive impairment and dementia by combining landmark cohort studies involving Aboriginal and Torres Strait Islander participants. The Kimberley Healthy Adults Project (KHAP), Koori Growing Old Well Study (KGOWS) and the Torres Strait Dementia Prevalence Study (TSDPS) share similar study methodologies and outcome measures that allow for harmonisation to examine both risk and protective factors of brain health and impairment in a larger combined cohort that may offer greater insights through enhanced diversity and statistical capability.

Primary outcomes:

Elucidate risk and protective factors associated with dementia and/or cognitive impairment in a combined cross-sectional dataset of Aboriginal and Torres Strait Islander participants.Elucidate risk and protective factors associated with incident dementia and/or cognitive impairment in a combined longitudinal dataset of Aboriginal and Torres Strait Islander participants.

Secondary outcomes:

Identify items in the Kimberley Indigenous Cognitive Assessment (KICA) or modified KICA (mKICA) that are most sensitive for dementia or cognitive impairment in the harmonised cross-sectional dataset.

## Methods/design

### Design

The KHAP study was undertaken from 2004 to 2006 and involved 363 Aboriginal participants aged 45 and older from different communities in the remote Kimberley region of WA [1]. The KGOW study recruited 336 participants aged 60 and older from five Aboriginal communities, two from metropolitan Sydney and three in regional coastal areas of NSW between 2010 and 2012 [14]. Follow-up of participants occurred after six and seven years for KGOWS-II and KHAP wave 2, respectively. The TSDP study was conducted between 2015 and 2018 and recruited 274 participants aged 45 and older from five mainland and 18 island communities across the Torres Strait and Northern Peninsula [3]. A summary of the studies and number of participants is provided in Table 1. All three cohort studies worked in partnership with local community organisations and Aboriginal and Torres Strait Islander members and researchers to support recruitment, data collection, and feedback to communities to ensure culturally safe engagement with participants. Risk factors were collected using a structured interview protocol and encompassed demographic, medical, and psychosocial factors collected from participants and family carers where available. This comprehensive assessment was independently evaluated by a panel of clinical specialists to establish clinical diagnoses by consensus. All three cohort studies used the KICA, a screening tool for older Aboriginal and Torres Strait Islander peoples, that was validated in the remote Kimberley region of WA [15], modified for urban and regional dwellers in the form of the mKICA [16] and adapted for the Torres Strait [17]. A shortened version (KICA-Screen) has been validated for face-to-face and telehealth administration [17, 18].

**Table 1 Tab1:** Descriptive summary of landmark studies

Study/Cohort	Location	Age (years)	Sample Size (*N*=)	Participants (*n*=)
Kimberley Healthy Adults Project (KHAP)				
Wave 1 (W1) 2004–2006 [1, 8]	Remote WA	≥ 45	363	289 with normal cognition; 45 with dementia; 29 with CIND*.
Wave 2 (W2) 2011–2013 [9]	Remote WA	≥ 45	398‡	. Of 363 W1 participants, 184 completed all W2 assessments, 5 had cognitive assessment only, 109 had died and 65 declined to participate or could not be located. 105 new participants were recruited at W2. W2 cohort: 226 with normal cognition; 29 with dementia; 33 with CIND; 1 missing diagnosis; had 109 died.
Koori Growing Old Well Study (KGOWS)				
Wave 1 (W1) 2010–2012 [2, 14, 19]	Urban & Regional NSW	≥ 60	336	249 with normal cognition; 45 with dementia; 38 with MCI†; 4 with other cognitive disorder.
Wave 2 (W2) 2016–2018 [20]	Urban & Regional NSW	≥ 60	233‡	Of 336 W1 participants, 165 were followed-up, 68 had died and 103 did not participate. W2 cohort: 105 with normal cognition; 10 with dementia at baseline; 16 with incident dementia; 34 with MCI; 68 had died.
Torres Strait Dementia Prevalence Study (TSDPS)				
Wave 1 (W1) 2015–2018 [3, 12]	Torres Strait	≥ 45	274	175 with normal cognition; 39 dementia; 60 CIND.

CIND = Cognitive Impairment No Dementia; MCI = Mild Cognitive Impairment; NSW = New South Wales; WA = Western Australia

*CIND is defined as those with a decrement in cognitive functioning that met DSM-IV-TR criteria for a cognitive or amnestic disorder but without significant loss in activities of daily living (ADL) and not attributable to a psychiatric illness or intellectual disability

† MCI diagnoses in the KGOW cohort were reclassified as CIND based on DSM IV-TR diagnoses in line with the other cohorts for analyses

‡ Sample sizes include those who have died

